**Methods:**

This is a prospective, interventional, single-center study designed to assess the effectiveness of bempedoic acid in achieving LDL-C targets in patients following ST-elevation or non-ST-elevation myocardial infarction who remain insufficiently treated with atorvastatin plus ezetimibe. Patients not previously treated with lipid-lowering agents and presenting with admission LDL-C > 2.6 mmol/L (100 mg/dL) will be treated with atorvastatin (at least 40 mg/day or equivalent) plus ezetimibe (10 mg/day) for 6 weeks. Thereafter, the subgroup of patients failing to reach an LDL-C < 1.4 mmol/L (55 mg/dL) will be escalated to additive bempedoic acid (180 mg/day) for another 8 weeks. Those who reach the target will continue the aforementioned therapy. The primary endpoint is the proportion of patients who successfully achieve an LDL-C < 1.4 mmol/L (55 mg/dL) after 8 weeks of treatment with triple therapy. Secondary endpoints include the proportion of patients successfully reaching the target in the overall population and in the background medication group alone.

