We planned and initiated the HAnnover ChOlesterol Lowering in Acute Coronary Syndrome (HACOL-ACS) trial to address three major clinically relevant questions: First, how many patients after a myocardial infarction reach the guideline-recommended target [LDL-C < 1.4 mmol/L (55 mg/dL)] on dual therapy with atorvastatin (at least 40 mg/day or equivalent) plus ezetimibe (10 mg/day)? Second, how many of the patients not achieving the target on a dual statin/ezetimibe therapy reach the target after adding bempedoic acid? Third, how many patients miss the target despite escalated oral triple lipid-lowering therapy and therefore need referral for PCSK9 inhibition? Our trial is distinct from the ES-BempedACS trial, as it focuses exclusively on patients without previous lipid-lowering therapy and will demonstrate the exact additive impact of bempedoic acid on top of dual therapy in each patient due to its sequential escalation strategy. Thereby, we will evaluate the real-world, guideline-mandated stepwise oral escalation therapy and quantify the residual unmet need for LDL-C target achievement. Starting with dual background medication is consistent with current guideline recommendations (17), and sequential add-on with bempedoic acid is also guideline-recommended (17), although this approach has never been tested in clinical practice. It is therefore important to document the efficacy of additive bempedoic acid on top of established and tolerated high-intensity statin treatment in combination with ezetimibe, to provide data supporting such recommendations. This is particularly important for the trial to be conducted in a sequential and clear manner as recent data from the ES-BempedACS trial with varying pretreatment populations did not show an additive LDL-C-lowering effect of bempedoic acid (15). Similarly, data from a recent oral PCSK9 inhibitor trial showed only a marginal additive effect in the bempedoic acid-treated comparator group when added to stable statin therapy (18).

The results of HACOL-ACS will also provide meaningful information for patients beyond the German healthcare system. While the trial design is adapted to national settings, the proportion of patients achieving guideline-recommended LDL-C targets at the end of the trial with double and triple therapies will be applicable both in regions with sequential dose escalations and in those allowing triple therapy from the beginning.

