**Figure 1 F1:**
[figure not shown]
Study algorithm. eGFR, estimated glomerular filtration rate; Hx, History of …; LDL-C, low-density lipoprotein-cholesterol; NSTEMI, Non-ST-segment myocardial infarction; STEMI, ST-segment myocardial infarction.

Group A will consist of the subgroup of patients who do not reach the LDL-C guideline target [LDL-C < 1.4 mmol/L (55 mg/dL)] after 6 weeks and will receive additive bempedoic acid (180 mg/day) for another 8 weeks (Triple therapy). Group B will consist of the subgroup of patients who achieve the LDL-C guideline target after 6 weeks of treatment with atorvastatin plus ezetimibe and who will continue on dual therapy for another 8 weeks (Dual therapy).

The 6-week escalation interval reflects local healthcare system, including certain reimbursement constraints, while aligning with evidence-based preferences to minimize delays in treatment intensification.

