#### Study endpoints

The primary endpoint is defined as the proportion of patients (%) in Group A who successfully achieve the European Society of Cardiology (ESC) LDL-C guideline target after Stage II. Secondary endpoints comprise the following: proportion of patients (%) who successfully achieve ESC LDL-C guideline targets [LDL-C < 1.4 mmol/L (55 mg/dL)] after treatment with dual therapy including atorvastatin (at least 40 mg/day or equivalent) plus ezetimibe (10 mg/day) at 6 and at 14 weeks; the proportion of patients (%) who successfully achieve the ESC LDL-C guideline targets after 14 weeks of treatment; the proportion of patients (%) who achieve American heart Association (AHA)/American College of Cardiology (ACC) guideline-recommended treatment targets of LDL-C < 1.8 mmol/L (70 mg/dL) after 14 weeks of treatment in the triple therapy group; mean change from baseline to week 6 and week 14 in LDL-C, total cholesterol, HDL-C, triglycerides, uric acid, creatine kinase, systolic and diastolic blood pressure, and heart rate; the proportion of non-compliant patients (%) taking less than 90% of the allocated study medication; and mean change from baseline to week 6 and to week 14 in quality of life.

Safety will be assessed by monitoring and recording all adverse events, serious adverse events, and certain laboratory parameters (further described under pharmacovigilance).

The primary endpoint was chosen to focus on the efficacy of the investigational compound in order to prevent that a higher than anticipated achievement rate of the LDL-C target on the baseline medication might result in an escalation subgroup being too small to conduct proper statistical analyses.

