## Statistical analysis

All analyses will be descriptive and performed in the ITT population. Demographic and baseline measurements will be summarized using descriptive methods. In the primary analysis, the proportion of responders and an exact descriptive 95% Clopper–Pearson confidence interval (CI) will be calculated. Patients with missing values for the primary endpoint will be counted as treatment failures in the ITT analysis, that is, as patients who did not achieve LDL-C guideline targets of <1.4 mmol/L (55 mg/dL) after treatment for 14 weeks.

Explanatory analyses for secondary endpoints will be carried out separately for Groups A and B. Responder rates will be examined using the exact 95% Clopper–Pearson CIs, and continuous data will be compared exploratorily using two-sided paired *t*-tests, with a two-sided level significance of 5%. In addition, mean changes in continuous laboratory parameters will be compared between Groups A and B using an analysis of covariance model, including baseline values at the start of the study and group assignment.

For the primary endpoint, a subgroup analysis will be carried out. Patients in the triple therapy group who fail to achieve the LDL-C guideline target of LDL-C < 1.4 mmol/L (55 mg/dL) after Stage I will be divided into four subgroups depending on their LDL-C level:
Group: LDL-C of 55 – ≤ 68.75 mg/dL (1.4–≤1.8 mmol/L).Group: LDL-C of 68.75 – ≤ 82.5 mg/dL (1.8–≤2.1 mmol/L).Group: LDL-C of 82.5 – ≤ 96.25 mg/dL (2.1–≤2.5 mmol/L).Group: LDL-C of 96.25 – ≤ 110 mg/dL (2.5–≤2.8 mmol/L).In every subgroup, the proportion of responders will be examined and exact 95% Clopper–Pearson CIs will be calculated. To evaluate the robustness of the results, efficacy analyses will be repeated in the PP population (sensitivity analyses).

Descriptive analyses will be performed to assess adverse events and serious adverse events. As this is an exploratory study, no adjustment for multiplicity will be performed. Confidence intervals and respective *p*-value will only be assessed descriptively.

Access to the final trial dataset will be centralized at the Center for Clinical Trials.

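### The by-group rule for secondary endpoints does not fit the week-6 target rate or the overall target rate, because Groups A and B are formed on the week-6 LDL-C result, and the denominator for an overall rate is not fixed.

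*Protocol article*

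**What the plan says.** **Analysis rule.** Protocol article, Statistical analysis: "Explanatory analyses for secondary endpoints will be carried out separately for Groups A and B". For proportions it adds: "Responder rates will be examined using the exact 95% Clopper–Pearson CIs". Continuous data are tested by paired t-test. Mean changes in continuous laboratory parameters are also compared between Groups A and B by ANCOVA on baseline and group; the time point is not named. All analyses are said to use the ITT population. The rule that a missing value counts as failure is written for the primary endpoint only.

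**Group definitions.** Study design, text under Figure 1: "Group A will consist of the subgroup of patients who do not reach the LDL-C guideline target" after 6 weeks, and "Group B will consist of the subgroup of patients who achieve the LDL-C guideline target after 6 weeks of treatment". The Study intervention/treatment section instead limits Group A to a week-6 LDL-C of 1.4 to 2.8 mmol/L and refers patients above 2.8 mmol/L for treatment outside the trial. Under Table 1, note a, only patients at or below 2.8 mmol/L return for V3.

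**Endpoints affected.** Study endpoints lists the dual-therapy target rate "at 6 and at 14 weeks; the proportion of patients (%) who successfully achieve the ESC LDL-C guideline targets after 14 weeks of treatment", and mean changes from baseline to weeks 6 and 14. The Abstract names "the proportion of patients successfully reaching the target in the overall population" as a secondary endpoint. The first of the three questions in the Background is "how many patients after a myocardial infarction reach the guideline-recommended target" on dual therapy.

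**The concern.** Group membership is the week-6 outcome. A rule that splits every patient by that outcome cannot then estimate how often the outcome occurs: each group's week-6 rate is known before any data are seen. The rule also has no place for a rate over the whole population, although the endpoint text asks for one.

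The continuous week-6 endpoints have a related problem. All patients are on dual therapy from baseline to week 6. Splitting them on the week-6 LDL-C puts those with low values in Group B and those with high values in Group A. The mean change in each group then reflects that selection as well as the treatment, and adjusting for baseline does not remove it.

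At stake are the answer to the trial's first question and the overall rate named in the Abstract. If the denominator is chosen only after the data are seen, the reported rate will depend on that choice.

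**Working it through.** **The plan's own figure.** The exact two-sided 95% Clopper–Pearson interval for 30/60 is 36.8 to 63.2%, a width of 26.4 points. This reproduces the sample-size statement, and 2 × 60 + 15 = 135 is correct. Neither is disputed here.

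**Step 1: week-6 rate under the stated rule.** Inputs: 135 enrolled (maximum, Sample size section) and about half at target after Stage I (same section). Take 67 in Group B and 68 in Group A.
- Group A: 0/68 = 0%. Upper limit 1 − 0.025^(1/68) = 5.3%.
- Group B: 67/67 = 100%. Lower limit 0.025^(1/67) = 94.6%.

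Both proportions are fixed by definition and carry no information.

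**Step 2: the quantity the first question asks for.** Number at target divided by number enrolled: 67/135 = 49.6%, exact 95% CI 40.9 to 58.4%, width 17.4 points.

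**Step 3: the denominator.** Two sets of patients are unplaced.
- Above 2.8 mmol/L at week 6: in Group A by the text under Figure 1, outside it by the Study intervention/treatment section.
- No V2 value: in neither group, and not covered by the missing-value rule.

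The documents do not give the share above 2.8 mmol/L. Assuming 2, 5 or 10% of 135 (3, 7 or 14 patients), and using only Groups A and B as treated:

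| Left out | Rate | Exact 95% CI |
|---|---|---|
| 0 | 67/135 = 49.6% | 40.9 to 58.4% |
| 3 | 67/132 = 50.8% | 41.9 to 59.6% |
| 7 | 67/128 = 52.3% | 43.3 to 61.2% |
| 14 | 67/121 = 55.4% | 46.1 to 64.4% |

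The shift is 1.1 to 5.7 points. Patients lost before V2 act in the same way: the stated 5% drop-out is about 7 of 135, and if all of it fell before V2 the third row would apply.

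**Step 4: week-6 LDL-C change by group (illustration).** Baseline is normal with mean 149 and SD 27 mg/dL (the earlier institutional cohort cited under Study population and inclusion), truncated above 100 mg/dL. The log ratio of week 6 to baseline is normal, centred so that half fall below 55 mg/dL. Its SD is not in the documents and is assumed to be 0.25, 0.35 or 0.45. Group A is 55 to 110 mg/dL. Simulated with about 1.9 million patients:

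| SD of log ratio | All | Group A | Group B | B minus A |
|---|---|---|---|---|
| 0.25 | −62.0% | −56.2% | −68.2% | −12.0 points |
| 0.35 | −60.8% | −53.2% | −70.5% | −17.3 points |
| 0.45 | −59.2% | −51.1% | −72.5% | −21.4 points |

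An ANCOVA of the week-6 change on baseline and group, in the same simulation, gives a baseline-adjusted A-versus-B difference of about 23 to 35 mg/dL, although both groups have had the same treatment. Neither group's mean equals the mean over all patients.

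**The case against.** The strongest reply is that this is a wording mismatch. The rule does not say that it covers every secondary endpoint, the Abstract commits to an overall-population rate, and Study endpoints restricts an item to the triple therapy group where that is meant. Nobody would report 0% and 100% as results. The number in Group B over the number enrolled gives the rate with an exact interval.

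Much of this stands. A reader might infer that the first question cannot be answered, or that no overall rate will be calculated. The documents do not support either: the counts are collected and the overall endpoint is named. What remains is that the only stated rule does not produce these estimates and that the denominator needed to recover them is open. A general reference to ITT does not say how patients above 2.8 mmol/L or without a V2 value are counted.

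On the week-6 changes, a reader might call the whole 12 to 21 point gap an artefact. That goes too far. The spread is assumed, and the simulation does not separate true differences in response from measurement noise. Describing the week-6 change in those who escalate and those who do not is also legitimate. What stands is that neither group mean, nor their contrast, estimates the effect of dual therapy.

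A full analysis plan may settle these points, but it is not shown. The published rule and the published endpoints still disagree.

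**Conclusion.** The concern holds as a rule that misfits some of its endpoints. For the week-6 target rate the by-group result is 0% and 100% by construction, against an intended estimate of about 49.6% (40.9 to 58.4%) at 135 patients and the article's assumed half at target. For the overall rate no matching analysis is stated, and the denominator choice moves the week-6 figure to between 50.8 and 55.4% if 2 to 10% of patients exceed 2.8 mmol/L and are left out. That share is an assumption.

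Within-group and between-group analyses of the baseline-to-week-6 LDL-C change are selected on their own outcome; the size of the distortion cannot be fixed from the documents. By-group analysis remains sensible for week-14 endpoints such as the below-1.8 mmol/L rate on triple therapy. The primary endpoint, sample size and data collection are untouched.

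**What to change.** Amend the secondary-endpoint paragraph of the Statistical analysis section before the data are analysed:

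1. Estimate the week-6 dual-therapy target rate and the overall week-14 target rate in all enrolled (ITT) patients, with exact 95% Clopper–Pearson intervals. Keep patients without an LDL-C value, and those referred out above 2.8 mmol/L at week 6, in the denominator as not at target.
2. Estimate baseline-to-week-6 mean changes in all enrolled patients with a week-6 value. Counting missing values as failures applies to the target rates, not to the means. Week-6 summaries by group are descriptive only, without a between-group ANCOVA.
3. Keep by-group analysis for the week-14 endpoints.
4. Reconcile the Group A definition in the text under Figure 1 with the one in the Study intervention/treatment section. This point does not turn on which is adopted.

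The cost is one paragraph, with no new patients, visits or measurements. The overall rates will look slightly less favourable than with a denominator of Groups A and B only, by 1.1 to 5.7 points at week 6 under the assumptions above.

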## Background

Low-density lipoprotein cholesterol (LDL-C) is one of the most important modifiable cardiovascular risk factors (1). In 2019, European guidelines lowered the recommended target LDL-C from <1.8 mmol/L (70 mg/dL) to <1.4 mmol/L (55 mg/dL) for secondary prevention in coronary artery disease (2). Despite well-intended recommendations and strong evidence, the previous LDL-C target of <1.8 mmol/L (70 mg/dL) had only been achieved in 21% in of patients included in registries (3, 4). In Germany, the reported proportion was even lower, with ≤15% of patients achieving the target following an acute coronary syndrome (5, 6).

After broader availability of more potent statins such as atorvastatin and rosuvastatin, we recently assessed the achievement of LDL-C guideline targets in real-world everyday clinical practice postmyocardial infarction. In brief, early standardized potent lipid-lowering therapy with atorvastatin plus ezetimibe resulted in nearly every second patient discharged after ST-elevation myocardial infarction (STEMI) achieving an LDL-C < 1.4 mmol/L (55 mg/dL) (7), with even higher rates in those receiving high-dose potent statins combined with ezetimibe (8).

In addition to high-intensity potent statins plus ezetimibe, proprotein convertase subtilisin/kexin type 9 (PCSK9) inhibitors such as evolocumab or alirocumab have shown additive clinical benefit in cardiovascular outcome trials (9, 10), but are not widely available for the overall population due to prescription limitations. In Germany, oral combination therapy must be escalated to the maximum level with documented inefficiency to reach the guideline-recommended LDL-C target prior to prescription of PCSK9 inhibitors. In the meantime, bempedoic acid has demonstrated a significant reduction in cardiovascular events when used as an oral add-on therapy in case of statin intolerance (11). Beyond that, adding bempedoic acid to maximally tolerated statins in high-cardiovascular-risk patients results in a further reduction of LDL-C by 17% (12). Therefore, bempedoic acid may offer a potential option to achieve guideline-recommended LDL-C targets <1.4 mmol/L (55 mg/dL) when standard combinations of a potent statin and ezetimibe are insufficient, and is currently required as part of stepwise escalation treatment prior to PCSK9 inhibition.

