## Limitations

The study has a single-center, open-label, non-randomized design, which introduces potential bias. For example, the single-arm design inherits the risk that changes in food intake, general lifestyle, and background medication over time may influence LDL-C and, thereby, the estimate of LDL-C-lowering effects of bempedoic acid. Hence, our study is exploratory regarding the escalation strategy and non-comparative.

HACOL-ACS is a short-term feasibility trial testing the applicability of sequential add-on bempedoic acid when guideline-recommended LDL-C targets are not achieved with tolerated high-intensity statin treatment combined with ezetimibe. The purpose of the trial is to describe the extent of additive LDL-C lowering provided by the sequential escalation. Given the small sample size and short duration, the trial does not assess long-term outcomes and, therefore, relies on surrogate endpoints, limiting clinical inference.

The single-center design and the fact that the study will be conducted within a specific healthcare system with defined prescribing constraints will impact but not prevent external validity and applicability to other settings. However, these prescribing constraints would have similar applicability even in a multicenter trial in a single country. The constraints on lipid-lowering therapy, however, allowed for prescription of atorvastatin, rosuvastatin, and ezetimibe, which will allow to use the most potent statins.

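### Triglycerides and creatine kinase would be better analysed on the log scale than as plain mean changes, and creatine kinase safety needs counts above the upper limit and a V2-to-V3 change

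*Protocol article*

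**What the plan says.** Under Study endpoints, the secondary endpoints include "mean change from baseline to week 6 and week 14 in LDL-C, total cholesterol, HDL-C, triglycerides, uric acid, creatine kinase", followed by blood pressure and heart rate. Under Statistical analysis, "continuous data will be compared exploratorily using two-sided paired" *t*-tests, "with a two-sided level significance of 5"%. The same section adds that "mean changes in continuous laboratory parameters will be compared between Groups A and B using an analysis of covariance model", with the study-start value and group as terms. No percent change, log transformation or rank method is named for any of these variables.

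The section also limits what these analyses are for. It states that "All analyses will be descriptive and performed in the ITT population", and that a *p*-"value will only be assessed descriptively".

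Three other places bear on the point:
- Background cites an earlier trial in which adding bempedoic acid to a statin "results in a further reduction of LDL-C by 17"%.
- Limitations gives the trial's purpose as to "describe the extent of additive LDL-C lowering" from sequential escalation.
- Table 1 takes lipids, uric acid and creatine kinase at screening, V2 and V3. Its note c lets the screening value be the routine admission sample.

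**The concern.** One summary and one test are applied to variables that probably behave differently. Triglycerides and creatine kinase usually have a long right tail and a spread that grows with the level. An arithmetic mean change then leans on the few patients with the largest values, and its confidence interval is wider than it needs to be. In a descriptive trial the summary is itself the result, so its scale matters even though no decision hangs on the *p*-value.

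Creatine kinase raises a second issue. The Pharmacovigilance section counts it among the safety measurements, next to muscle-related effects. What matters there is a clear rise in a few patients, which a group mean is poorly suited to show. A baseline drawn during the index infarction makes this worse, because the expected change from it is a fall.

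For LDL-C the issue is only comparability. The one effect size the article gives for the add-on drug is relative, while an absolute mean change depends on the LDL-C mix of the group.

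**Working it through.** **The plan's own figure.** No sample size, SD or power is given for a continuous endpoint. The only planning figure is 60 patients in the triple therapy group, for a 95% Clopper–Pearson width of 26.4% at *p* = 0.5. With 30 of 60 responders the interval is 0.3681 to 0.6319, width 0.2639. The figure reproduces, and *n* = 60 is used below.

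**Triglycerides and creatine kinase: method.** All SDs, correlations and effects here are assumptions. Values are lognormal with log SD *s* at each visit, correlation *r* between visits and true ratio *m*. The standardised effect of the paired test is
- log scale: |ln *m*|·√*n* / [*s*·√(2(1−*r*))]
- raw scale: |*m*−1|·√*n* / √[(1+*m*²)(e^(*s*²)−1) − 2*m*(e^(*r s*²)−1)]

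Example, triglycerides with *s* = 0.5, *r* = 0.6, *m* = 0.85:
- log: 0.1625 × 7.746 / 0.4472 = 2.81
- raw: 0.15 × 7.746 / √(1.7225 × 0.2840 − 1.70 × 0.1618) = 0.15 × 7.746 / 0.4627 = 2.51

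**Simulated power** (20,000 trials, two-sided 5%):

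| Variable | log SD, correlation | Change | Raw | Log | Loss (points) |
|---|---|---|---|---|---|
| Triglycerides | 0.4, 0.6 | −15% | 0.91 | 0.94 | 3 |
| Triglycerides | 0.5, 0.6 | −15% | 0.71 | 0.79 | 8 |
| Triglycerides | 0.6, 0.6 | −15% | 0.53 | 0.63 | 11 |
| Creatine kinase | 0.5, 0.6 | +15% | 0.59 | 0.67 | 8 |
| Creatine kinase | 0.7, 0.6 | +20% | 0.47 | 0.61 | 14 |
| Creatine kinase | 1.0, 0.5 | +30% | 0.31 | 0.52 | 21 |
| Creatine kinase | 1.2, 0.3 | +30% | 0.16 | 0.29 | 13 |

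A second parametrisation uses separate between- and within-person log SDs:
- triglycerides 0.5/0.25, −10%: 52% raw, 62% log
- triglycerides 0.6/0.3, −15%: 68% raw, 83% log
- creatine kinase 0.6/0.4, +20%: 53% raw, 69% log

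In the tabulated scenarios the three largest of 60 changes carry 35–44% of the sum of squares for triglycerides and 40–66% for creatine kinase. Type I error of the raw test is 0.042–0.049, so it is not inflated.

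**LDL-C, V2 to V3.** Group A values at V2 are taken as uniform on 1.4–2.8 mmol/L, with a 17% fall. Raw versus percent change:
- log SD of change 0.15: power 1.00 and 1.00
- log SD 0.25: 0.995 and 0.996
- log SD 0.35: 0.77 and 0.78

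The loss is at most about 1.5 points, because Group A spans only a twofold range. The same relative effect is 0.17 × 55 = 9 mg/dL at the bottom of that range and 0.17 × 110 = 19 mg/dL at the top, so the absolute mean depends on case mix.

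**Creatine kinase rises in a few patients.** Let 2 of 60 patients change by *d* and the rest not at all. The mean is 2*d*/60 = 0.0333*d*. The SD is *d*·√[(2 − 4/60)/59] = 0.181*d*. So *t* = 0.0333 / (0.181/√60) = 1.43, short of the critical value of about 2.00 whatever *d* is, and the same holds for two equal changes in logs. In simulation (median 110, between-person log SD 0.6, within-person 0 to 0.4, two patients at 2000), *p* < 0.05 occurs in 0–1.5% of runs on the raw scale and 0–9% on the log scale.

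**Infarct-level baseline.** Assume an admission median of 200–1000 U/L with log SD 0.9–1.2 and a later median of 110. Three of 60 patients then hold 22–30% of the baseline total. At median 600 and log SD 1.2 the mean change is −1066 against a median change of −479. Both scales show a significant fall in over 99% of runs. With an assumed baseline median of 500 and log SD 1, putting two patients at 2000 still leaves a significant fall in 99.9% of runs on the raw scale. At a much lower admission level the raw test shows the fall less often, but neither scale then shows the rise.

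**The case against.** The best case against is that this is a condensed article. Transformation and extra tables are usual content for an analysis plan that is not shown, and the article never says raw or absolute. That is fair, and if the full plan already specifies logs, the log-scale part of this point is met. But the article does more than stay silent: it defines the summary as a mean change and names the tests for all continuous data. It is reasonable to say that a better method exists for two of the variables.

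It also stands that skewness and every SD are assumed, that the analyses are labelled descriptive, and that safety rests mainly on adverse events and descriptive review rather than on a *t*-test.

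A reader might draw four stronger conclusions, which the document does not support:
- **The 17% is the plan's benchmark.** It is a result cited in Background. The plan's own yardstick is the responder rate at LDL-C below 1.4 mmol/L.
- **LDL-C analysis loses precision.** It hardly does, and percent change can be derived from the same data.
- **A few large values decide the trial's result.** The primary result is a binary proportion, and the raw test keeps its type I error.
- **A log transform repairs the creatine kinase safety check.** It does not. A mean test on either scale misses two rises in 60, and a geometric mean change from an infarct sample still mainly reflects recovery from the infarct.

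**Conclusion.** The point holds as a minor improvement to exploratory secondary analyses. Under assumed lognormal spread and 60 patients, plain mean changes cost about 3–15 points of power for triglycerides and 8–21 for creatine kinase, and a few patients dominate the mean change. The size depends on log SDs that the article does not give. These power figures assume a comparison between two stable visits. They do not describe creatine kinase change from an infarct admission sample, where the fall is large on either scale.

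For LDL-C the only gain from a percent scale is comparability with the relative effect the article cites. For creatine kinase as a safety measure, change of scale is not the remedy. Counts above the upper limit and the change from V2, when bempedoic acid starts, are.

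**What to change.** 1. Analyse triglycerides and creatine kinase on the log scale in both the paired tests and the analysis of covariance (log baseline as covariate). Report geometric mean percent change with 95% CI.
2. Keep the planned LDL-C summary and add percent change from V2 to V3 in Group A. State that it is for comparison with the cited relative effect. It stays descriptive, since Group A is selected on the V2 value and has no control.
3. For creatine kinase and uric acid, tabulate by group the number of patients above the laboratory's upper limit at V2 and at V3, and report the V2-to-V3 change.
4. Leave the other continuous variables and the primary analysis as they are.

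The cost is analysis wording, a little extra programming, and ratios in place of absolute units for two variables. No new data, visits or patients are needed. Trial status gives recruitment as running to March 2026, so the change should be fixed in writing before the data are analysed.
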